### 3.2 Experience with HIV-MAG

HIV-MAG, the HIV-1 multiantigen pDNA vaccine, alone or co-administered with GENEVAX® IL-12, given IM by electroporation or standard needle injection is currently being tested in HIV-infected individuals in the US, but no safety data are available yet (ACTG 5281).

Pre-clinical data in rabbits indicate that the 2 HIV-MAG pDNA constructs, expressing a Gag/Pol fusion protein, a Nef/Tat/Vif fusion protein and Env protein, co-administered with human IL-12 pDNA given either IM or IM/EP are well-tolerated and do not cause any adverse effects. No significant differences in biodistribution or persistence were observed when vaccine pDNA was administered by TDS-IM/EP or by conventional IM injection.

In another study in rabbits, repeated dosing with HIV-MAG with or without GENEVAX® IL-12 given IM/EP as prime followed by two doses of recombinant viral vector boost (Vesicular Stomatitis Virus vaccine [VSV HIV gag]) as boost was also well tolerated.

Preclinical immunogenicity studies in mice and rhesus macaques showed that the HIV-MAG co-administered with IL-12 by IM/EP was able to induce HIV-1 antigen specific cell-mediated immune (CMI) responses as determined by IFN- $\gamma$  ELISPOT assay. In macaques, each HIV-MAG pDNA construct co-administered with GENEVAX® IL-12 also elicited humoral immune responses measured by ELISA.

Please see the most recent version of the Profectus Biosciences, Inc. (PBS) HIV-MAG – IL12 Investigator's Brochure (Version 2.0, May 2011) for a full description of the preclinical safety profile of this candidate vaccine.

### 3.3 Experience with recombinant human IL-12 pDNA as molecular adjuvant for HIV pDNA vaccines

No clinical studies have yet been conducted testing HIV-MAG vaccine co-administered with GENEVAX® IL-12.

However, other HIV-1 pDNA vaccines expressing antigens similar to HIV-MAG have been tested in Phase 1 clinical studies in combination with GENEVAX® IL-12. The NIH-sponsored clinical trials (HVTN 060, 063, 070) in which different candidate HIV-1 pDNA vaccines co-administered with the GENEVAX® IL-12 given intramuscularly (IM) by needle injection were tested in approximately 250 healthy HIV-uninfected adults. No major safety concerns have been noted in these studies.

In HVTN 080, an HIV-1 pDNA vaccine (PENNVAX™-B gag, pol, env) mixed with GENEVAX® IL-12 was administered IM by *in vivo* electroporation (EP) using Inovio's Celectra device. Final safety data are not yet available, but no major safety concerns have been reported. Preliminary

immunogenicity data from HVTN 080 indicate that IL-12 increases the frequency of immune responses to the HIV-1 proteins as measured by ICS (CD4+: 81%, CD8+: 52% with IL-12 versus CD4+: 44%, CD8+: 33% without IL-12) 2 weeks post 3rd administration of PENNVAX™-B and GENEVAX® IL-12.

Please see the Profectus Biosciences Inc. (PBS) HIV-MAG – IL12 Investigator Brochure (Version 2.0, May 2011) for a full description of the preclinical and/or clinical safety profile of the HIV-MAG vaccine and the IL-12 pDNA as molecular adjuvant.

### 3.4 Experience with Ichor TriGrid™ Delivery System for *in vivo* electroporation

To date, the TDS-IM has been utilized as the means of DNA vaccine administration in two completed clinical trials and is currently being evaluated in three ongoing clinical studies. These studies include completed studies of a xenogeneic tyrosinase DNA vaccine candidate in patients with Stage IIB-IV melanoma and a multigenic HIV-1 DNA vaccine candidate (ADVAX) in healthy, HIV uninfected volunteers (IAVI C004). The currently ongoing clinical studies include testing of a multi-epitope malaria DNA vaccine in healthy volunteers, assessment of an epitope based TRP-2 melanoma vaccine in patients with AJCC stage III-IV melanoma, and a multi-antigen HIV DNA vaccine administered with or without a DNA based human IL-12 adjuvant in HIV infected individuals. To date, the five trials have enrolled over 90 subjects in electroporation arms of the studies (including subjects receiving either the DNA vaccine candidate or placebo). The device has been used for administration at DNA doses of up to 4.0 mg. Subjects have been administered the vaccine either as a single injection in one muscle site or as two injections in two separate muscle sites. To date, subjects administered the DNA dose as a single injection have received up to five administrations (i.e., five total TDS-IM injections) while subjects administered the DNA dose in two injections have received up to four administrations (i.e., eight total TDS-IM injections).

### 3.5 Experience with Ad35-GRIN/ENV

Ad35-GRIN/ENV consists of two co-formulated Ad35 vectors:

- Ad35-GRIN is a replication-incompetent, recombinant Adenovirus serotype 35 expressing HIV-1 Clade A genes (*gag*, *reverse transcriptase*, *integrase* and *nef* (GRIN).
- Ad35-ENV is a replication-incompetent, recombinant Adenovirus serotype 35 expressing HIV-1 clade A gp 140 gene (ENV).

A Phase 1 placebo-controlled, double-blinded, randomized dose-escalation trial (IAVI B001) to evaluate the safety and immunogenicity of Ad35-GRIN/ENV HIV vaccine at three dosage levels (Group A:  $2 \times 10^9$  vp, Group B:  $2 \times 10^{10}$  vp, and Group C:  $2 \times 10^{11}$  vp) and Group D: Ad35-GRIN vaccine at the dosage of  $1 \times 10^{10}$  vp is being conducted. Vaccine is administered intramuscularly at months 0 and 6. Each of the four groups of 14 Ad35 seronegative volunteers includes 10 vaccine and 4 placebo recipients for a total of 56 volunteers.

No related serious adverse event has been reported to date. Reactogenicity events reported seem dose-dependent. Local reactogenicity events are mostly pain and tenderness at the site of injection, mostly mild or moderate in Group A, B, and D volunteers and mild to severe in Group C volunteers. Systemic reactogenicity events reported included chills, fever, malaise, headache, myalgia, and arthralgia. These reactions were predominantly mild or moderate, except in Group C, in which more severe events were observed. All reactogenicity events were transient and resolved spontaneously.

In total, 165 non-serious adverse events have been reported (as of May 5, 2011). The frequency was not dose-related. Two events were assessed as severe (Grade 3): deep vein thrombosis and anxiety disorder; both were considered unrelated to the vaccine. Fifty-eight (58) events were assessed as moderate (Grade 2) in severity: only one was considered possibly related to vaccine (influenza-like illness). One hundred and five (105) events were assessed as mild (Grade 1) in severity. Nine events were considered as possibly related to vaccine (diarrhea, injection site haemorrhage, influenza-like illness, upper respiratory tract infection, 2 nasal congestions, pharyngo-laryngeal pain, pharyngitis, and naso-pharyngitis), one as probably related (injection site anesthesia) and one definitely related (injection site swelling). All other events were considered unrelated or unlikely related to vaccine.

Moderate or greater abnormal clinical laboratory values were observed in five volunteers: elevated AST in two subjects, low haemoglobin in two women (all moderate and not considered as related to vaccination), and elevated ALT in one subject (severe and not considered as related to vaccination).

Two other Phase 1 double-blinded, placebo-controlled, randomized trials in HIV-uninfected, healthy adult volunteers are currently ongoing testing the two Ad35 HIV-1 vaccine vectors separately each:

- IAVI B002 at four Clinical Research Centres (CRCs) evaluating the safety and immunogenicity of Ad35-GRIN given as either as prime or as boost or co-administered with an adjuvanted HIV protein vaccine;
- IAVI B003 at seven CRCs testing Ad35-EnvA in homologous and heterologous prime-boost combinations with Ad26ENVA.01. No data are available yet.

Please see the most recent version of the Ad35-GRIN/ENV Investigator's Brochure (Version 4.0, 29 June 2011) for a full description of the preclinical and clinical safety profile of this candidate vaccine.

## 4.0 STUDY OBJECTIVES

### 4.1 Primary Objectives

1. To evaluate the safety and tolerability of HIV-MAG with or without co-administered GENEVAX® IL-12 given intramuscularly by *in vivo* electroporation (IM/EP) using the Ichor Medical Systems TriGrid™ Delivery System (TDS-IM), followed by Ad35-GRIN/ENV in each of four different regimens
2. To evaluate the safety and tolerability of Ad35-GRIN/ENV followed by HIV-MAG with co-administered GENEVAX® IL-12 given intramuscularly by *in vivo* electroporation (IM/EP) using the Ichor Medical Systems TriGrid™ Delivery System (TDS-IM)

### 4.2 Secondary Objectives

1. To determine whether the HIV-specific immune responses induced by HIV-MAG are increased by co-administration of GENEVAX® IL-12 in a prime-boost regimen with Ad35-GRIN/ENV given as boost and if so, which dosage level induces the higher immune responses
2. To compare HIV-specific immune responses induced by HIV-MAG co-administered with GENEVAX® IL-12 IM/EP once at M0 followed by Ad35-GRIN/ENV IM at M4 with those induced by HIV-MAG co-administered with GENEVAX® IL-12 IM/EP trice at M0,1,2 followed by Ad35-GRIN/ENV IM at M6
3. To compare HIV-specific immune responses induced by Ad35-GRIN/ENV IM prime at M0 followed by HIV-MAG co-administered with GENEVAX® IL-12 IM/EP boost at M4 with those induced by HIV-MAG co-administered with GENEVAX® IL-12 IM/EP prime at M0 followed by Ad35-GRIN/ENV IM boost at M4

## 5.0 STUDY ENDPOINTS AND STUDY DESIGN

### 5.1 Study Endpoints

#### 5.1.1 Primary Endpoints

##### *Safety and tolerability:*

To assess safety and tolerability of the different prime-boost regimens:

1. Proportion of volunteers with moderate or greater reactogenicity (i.e., solicited adverse events) during a 7 day follow-up period after each vaccination
2. Proportion of volunteers with moderate or greater and/or vaccine-related unsolicited adverse events (AEs) including safety laboratory (biochemical, haematological) parameters, from the day of each vaccination up to 28 days post each vaccination.
3. Proportion of volunteers with vaccine related serious adverse events (SAEs) collected throughout the study period

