### **6.3 Post-Vaccination Visits**

The volunteer will be asked to maintain a Memory Aid from the day of each vaccination and for the next 7 days. Study staff will review the Memory Aid with the volunteer, determine the severity of the reactions through volunteer discussion and record the information on applicable source documentation. There will be scheduled clinic visits 3, 7 and 14 days after each vaccination for an assessment by clinic staff.

The following procedures will be conducted at these visits:

- Collect concomitant medication information
- If any signs or symptoms are present, perform a symptom-directed physical examination
- Assess any adverse events, including local and systemic reactogenicity
- Collect specimens for all tests as indicated in the Schedule of Procedures (Appendices A-B)

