## 9.0 ASSESSMENTS

### 9.1 Safety Assessments

Data on local and systemic reactogenicity (i.e., solicited AEs) will be collected by structured interview and medical examination. Volunteers will be given a Memory Aid,

which is a tool to assist with collecting reactogenicity data, but will not be saved as a source document. Data on other adverse events will be collected with open-ended questions. All data will be recorded on the appropriate source documents and entered into the study database.

Local and systemic reactogenicity events will be solicited by study staff prior to vaccination and at least 30 minutes post-vaccination, as specified in the Schedule of Procedures (Appendices A-B).

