#### **9.1.4 Other adverse events**

Other adverse events (AEs) will be collected through one month after the last vaccination in all groups. Serious Adverse Events (SAEs) will be collected throughout the entire study period. Open ended questions will be asked at time points according to the Schedule of Procedures (Appendices A-B). All adverse events will be graded using Appendix C, Adverse Event Severity Assessment Table, as a guideline and will be assessed for causality to the IP.

For more information regarding adverse events refer to Section 10.0, Adverse Events.

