## APPENDIX A: SCHEDULE OF PROCEDURES GROUPS 1-3

| Study Month                            |        | M0             |     |     |     | M1             |     |     |     | M2             |     |     |     | M3  | M5   | M6             |      |      |      | M7   | M9             | M12                    |
|----------------------------------------|--------|----------------|-----|-----|-----|----------------|-----|-----|-----|----------------|-----|-----|-----|-----|------|----------------|------|------|------|------|----------------|------------------------|
| Week                                   |        | W0             |     | W1  | W2  | W4             |     |     |     | W8             |     | W9  | W10 | W12 | W20  | W24            |      | W25  | W26  | W28  | W36            | W48 or ET  |
| Study Day                              | Screen | 0              | D3  | D7  | D14 | D28            | D31 | D35 | D42 | D56            | D59 | D63 | D70 | D84 | D140 | D168           | D171 | D175 | D182 | D196 | D252           | D336                   |
| Visit Windows (Days)                   |        | -42            | ± 1 | ± 3 | ± 3 | ± 3            | ± 1 | ± 3 | ± 3 | ± 3            | ± 1 | ± 3 | ± 3 | ± 3 | ± 3  | ± 7            | ± 1  | ± 3  | ± 3  | ± 3  | ± 7            | ± 7                    |
| Investigational Product         |        |                |     |     |     |                |     |     |     |                |     |     |     |     |      |                |      |      |      |      |                |                        |
| HIV-MAG + GENEVAX® IL12 Placebo        |        | X              |     |     |     | X              |     |     |     | X              |     |     |     |     |      |                |      |      |      |      |                |                        |
| Ad35-GRIN/ENV / Placebo                |        |                |     |     |     |                |     |     |     |                |     |     |     |     |      | X              |      |      |      |      |                |                        |
| Consent /Assessments/Counseling |        |                |     |     |     |                |     |     |     |                |     |     |     |     |      |                |      |      |      |      |                |                        |

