| Local and Systemic Reactogenicity      |        | X  | X   | X   |     | X  | X   | X   |     | X  | X   | X   |     |     |      | X  | X    | X    |      |      |                |                        |

| Study Month                                                                                   |        | M0  |     |     |     | M1  |     |     |     | M2  |     |     |     | M3             | M5   | M6   |      |      |      | M7             | M9   | M12                    |
|-----------------------------------------------------------------------------------------------|--------|-----|-----|-----|-----|-----|-----|-----|-----|-----|-----|-----|-----|----------------|------|------|------|------|------|----------------|------|------------------------|
| Week                                                                                          |        | W0  |     | W1  | W2  | W4  |     |     |     | W8  |     | W9  | W10 | W12            | W20  | W24  |      | W25  | W26  | W28            | W36  | W48 or ET  |
| Study Day                                                                                     | Screen | 0   | D3  | D7  | D14 | D28 | D31 | D35 | D42 | D56 | D59 | D63 | D70 | D84            | D140 | D168 | D171 | D175 | D182 | D196           | D252 | D336                   |
| Visit Windows (Days)                                                                          |        | -42 | ± 1 | ± 3 | ± 3 | ± 3 | ± 1 | ± 3 | ± 3 | ± 3 | ± 1 | ± 3 | ± 3 | ± 3            | ± 3  | ± 7  | ± 1  | ± 3  | ± 3  | ± 3            | ± 7  | ± 7                    |
|                                                                                               |        |     |     |     |     |     |     |     |     |     |     |     |     |                |      |      |      |      |      |                |      |                        |
| Adverse Events                                                                                |        | X   | X   | X   | X   | X   | X   | X   | X   | X   | X   | X   | X   | X              | X    | X    | X    | X    | X    | X              |      |                        |
| Serious Adverse Events                                                                        | X      | X   | X   | X   | X   | X   | X   | X   | X   | X   | X   | X   | X   | X              | X    | X    | X    | X    | X    | X              | X    | X                      |

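### Visit windows allow the visits that close the 7-day solicited period (every vaccination) and the final 28-day adverse event period to fall up to 3 days early, and Section 6.3 and the appendices disagree on Day 14.

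*Protocol*

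**What the plan says.** Section 5.1.1 gives the first primary endpoint as "Proportion of volunteers with moderate or greater reactogenicity (i.e., solicited adverse events) during a 7 day follow-up period after each vaccination". The second, on unsolicited adverse events, runs "from the day of each vaccination up to 28 days post each vaccination".

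The text and the schedule then describe how these periods are observed.

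- **Section 6.3:** "There will be scheduled clinic visits 3, 7 and 14 days after each vaccination for an assessment by clinic staff". The procedures listed for these visits include local and systemic reactogenicity. The volunteer keeps a Memory Aid from the day of vaccination through the following 7 days; staff go through it with the volunteer, grade the reactions and enter them in source documentation.
- **Section 9.1:** the Memory Aid is described as one "which is a tool to assist with collecting reactogenicity data, but will not be saved as a source document".
- **Sections 9.1.1 and 9.1.2:** reactogenicity is assessed at the time points in the Schedule of Procedures.
- **Appendices A and B:** the reactogenicity row is marked at the vaccination, Day-3 and Day-7 visits and is blank at Day 14. All Day-7 visits are ±3.
- **Section 9.1.4:** "Other adverse events (AEs) will be collected through one month after the last vaccination in all groups".
- **Appendices A and B, adverse event row:** the last mark is at D196 (Groups 1-3) or D140 (Groups 4-5), each ±3. Footnotes limit the interim history at later visits to capturing serious events.

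**The concern.** Both endpoints are defined over fixed periods, and the nominal visit days match those periods exactly. The windows are symmetric, however, so a site that follows the schedule may hold the closing visit before the period has ended.

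For the solicited endpoint, a Day-4 visit can be the last time the appendices ask for reactogenicity. A moderate reaction that begins on Day 6 then has no marked solicited assessment. If it is mentioned at Day 14 in answer to an open-ended question, it may be recorded as another adverse event and counted under the second endpoint instead of the first.

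For the unsolicited endpoint, a closing visit on Day 25 after the last vaccination leaves Days 26 to 28 with no scheduled collection of non-serious events.

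The groups are small. With 12 vaccine recipients in a group, one volunteer misclassified as event-free moves that group's vaccine-arm proportion by 1/12 = 8.3 percentage points. An event that is never collected can only lower the recorded proportion.

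**Working it through.** **Inputs.** Vaccination days are D0, D28, D56 and D168 for Groups 1-3 (Appendix A) and D0 and D112 for Groups 4-5 (Appendix B). The follow-up columns come from the same tables; for the Groups 1-3 boost, for example, they read "D168 | D171 | D175 | D182 | D196". Windows were matched to visit days column by column.

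**Step 1: reproduce the nominal periods.** Nominal interval = visit day − vaccination day.

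- Day-7 visits: 7−0, 35−28, 63−56, 175−168 and 119−112 all equal 7.
- 28-day visits: 28−0, 56−28, 84−56, 196−168 and 140−112 all equal 28.

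Nominally, the schedule matches both endpoint definitions after all six vaccinations.

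**Step 2: apply the windows.** Range = nominal interval ± window, counted from the actual vaccination, which is how Section 6.3 counts the follow-up visits.

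| Vaccination | Day-3 visit | Day-7 visit | 28-day visit | Next adverse event visit, earliest |
|---|---|---|---|---|
| Groups 1-3, M0 | Days 2-4 | Days 4-10 | Days 25-31 | Day 30 (D31 ±1) |
| Groups 1-3, M1 | Days 2-4 | Days 4-10 | Days 25-31 | Day 30 (D59 ±1) |
| Groups 1-3, M2 | Days 2-4 | Days 4-10 | Days 25-31 | Day 81 (D140 ±3) |
| Groups 1-3, M6 | Days 2-4 | Days 4-10 | Days 25-31 | none |
| Groups 4-5, M0 | Days 2-4 | Days 4-10 | Days 25-31 | Day 109 (D112 ±3) |
| Groups 4-5, M4 | Days 0-6 | Days 4-10 | Days 25-31 | none |

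**Step 3: worst case, solicited endpoint.** Earliest closing visit: 7 − 3 = Day 4. Days after it: 7 − 4 = 3, and 3/7 = 43%. This applies equally after all six vaccinations. Whether Day 14 recovers those days depends on which part of the protocol a site follows: Section 6.3 assesses reactogenicity there, while the appendices, to which Sections 9.1.1 and 9.1.2 defer, do not.

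**Step 4: worst case, unsolicited endpoint.** Earliest closing visit: 28 − 3 = Day 25. Days after it: 28 − 25 = 3, and 3/28 = 11%. The last column shows that a later visit with an adverse event mark follows every vaccination except the last and can pick up Days 26 to 28. After the last vaccination (M6 in Groups 1-3, M4 in Groups 4-5) none follows.

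**Step 5: D115.** With ±3 and a vaccination on D112, this visit may fall from D112 to D118, that is, Days 0 to 6. It may coincide with the vaccination day and overlaps the D119 window (D116 to D122). Every other Day-3 visit is ±1. D115 is not a closing visit, so this does not alter Steps 3 and 4.

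**The case against.** The best defence is that data for the exposed days have other routes into the record. The Memory Aid spans the full 7 days, and its content reaches source documents through staff review, so discarding the paper does not mean the days go unrecorded. Section 6.3 places reactogenicity at Day 14, and the appendices mark interim history and adverse events there. Section 6.5 allows unscheduled contacts, which are entered in the database. Section 9.1.4 itself requires collection for one month. The windows are symmetric, and nothing suggests visits will run early.

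Much of this stands, and it rules out several stronger readings that a reader might infer:

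- **That Days 5 to 7 are simply not recorded.** Section 6.3 provides a route. What is missing is a matching mark in the appendices, so the route depends on which part of the protocol is followed.
- **That the loss is greatest after the Groups 4-5 boost.** Its closing windows equal those after every other vaccination; only the D115 window differs.
- **That only 18 of 28 days might be observed after the Groups 1-3 boost.** This takes a boost at D175 (D168 ±7) and a closing visit at D193 (D196 − 3), with windows counted from study day 0. Section 6.3 counts the early follow-up visits from each vaccination and Section 9.1.4 counts from the last one. On a day-0 count the Day-3 visit could precede the boost.
- **That comparisons between regimens are distorted.** The closing windows are the same in all groups, and vaccine and placebo recipients within a group share one schedule.

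What the defence does not answer is that general collection wording and optional contacts do not replace a scheduled assessment. A compliant site may still make its last marked reactogenicity assessment on Day 4 and its last adverse event visit on Day 25.

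**Conclusion.** The point holds as a scheduling defect affecting two primary endpoints. After every vaccination, up to 3 of the 7 solicited days (43%) can follow the last reactogenicity assessment marked in the appendices, and the appendices conflict with Section 6.3 on whether Day 14 covers them. After the last vaccination only, up to 3 of 28 days (11%) can lack scheduled collection of non-serious events, contrary to Section 9.1.4. The wider D115 window is a separate inconsistency.

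These are the widest gaps the windows permit, not expected losses. They assume windows counted from the actual vaccination and visits held at the early limit; the 43% also assumes that the site follows the appendices rather than Section 6.3. The protocol gives no timing of events within the periods, so neither the number of events missed nor any resulting bias can be computed. The correction should be made because it is cheap and concerns primary endpoints, not because harm to the results has been shown.

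**What to change.** 1. In Appendices A and B, set the Day-7 visits (D7, D35, D63 and D175; D7 and D119) to -0/+3 days from the actual vaccination date. They then fall on Days 7 to 10, still before the Day-14 visit (Days 11 to 17).
2. Set the closing visits, D196 in Appendix A and D140 in Appendix B, to -0/+3 days from the actual last vaccination, giving Days 28 to 31. The D140 visit in Appendix A precedes the boost and is not affected.
3. Mark reactogenicity review, including transcription of the Memory Aid, at the Day-14 visits in both appendices so that they agree with Section 6.3. This also catches a reaction that starts late on Day 7, after the visit.
4. Make the D115 window consistent with the other Day-3 visits.

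This is a schedule edit and adds no visits. The cost is slightly less scheduling freedom for sites and a short reactogenicity review at a visit that already takes place.
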